### **13.3.2. Secondary outcomes efficacy assessment**

#### **13.3.2.1. Evaluation items**

- Stimulated SFR after 12 weeks of medication
- Differences and mean percentage changes in unstimulated and stimulated SFR from baseline (week 0) to the end of the trial (week 12)
- Differences and mean percentage change in the visual analogue scale (VAS) and 14-item Oral Health Impact Profile (OHIP-14), and from baseline (week 0) to the end of the trial (week 12).
- Differences and mean percentage changes in the uptake ratio (UR), maximum accumulation (MA), and maximum secretion (MS) on salivary scintigraphy from baseline (week 0) to the end of the trial (week 12).

#### **13.3.2.2. Statistical methods**

- To analyze the secondary outcomes, in the case of continuous outcome measures, a normality test for the distribution of data will be initially performed. In the case of non-normally distributed data, the data will be transformed to a normal distribution using the log-transformation or square root transformation methods.
- The analysis will proceed using either parametric or non-parametric methods. Specifically, an independent T test or Mann-Whitney U test will be performed to compare values between the two groups.
- The Paired T test or Wilcoxon signed-rank test will be performed to compare intragroup continuous values.
- The group and time interaction effect of repeated-measures data will be analyzed through repeated-measures analysis of variance (ANOVA) or ANCOVA, or through the GEE model test based on the nature of the data.
- The level of significance will be set at  $p < 0.05$ .

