## Version 2.6

- unstimulated SFR  $\leq$  0.25 ml/min
- VAS score for dry mouth over the past one month  $\geq$  4
- age  $>$ 19 years
- compliance with all written informed consent

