## **10.2. Evaluation of efficacy**

### **10.2.1. Salivary flow rate (SFR) test**

- Visit 2 (Week 0) is replaced by screening test.
- Evaluation at Visit 3 (Week 4), Visit 4 (Week 8), Visit 5 (Week 12).

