#### **13.3.1.2. Statistical methods**

- A 95% confidence interval (95% CI) will be used to analyze primary outcomes.
- We will calculate the 95% CI of the mean difference in the unstimulated SFR between the two groups after 12 weeks of medication. If the lower end of the 95% CI of the mean difference is greater than the non-inferiority limit ( $-0.21$ ), it will be concluded that the experimental group is not inferior to the control group.
- For further analysis, if the SFR between the two groups satisfy the normality test, a t-test will be performed to compare the two groups in terms of the primary outcomes; otherwise, the Mann-Whitney U test will be performed. If there is a significant difference in baseline values between the two groups, repeated-measures analysis of covariance (ANCOVA) will be performed.

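### Secondary outcomes are compared between arms without baseline adjustment, which gives up precision by an amount that depends on correlations the protocol does not state

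*Protocol*

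**What the plan says.** Section 13.3.2.1 lists the secondary outcomes. One is a plain week-12 value: "Stimulated SFR after 12 weeks of medication". The rest are changes, absolute and in percent: "Differences and mean percentage changes in unstimulated and stimulated SFR from baseline (week 0) to the end of the trial (week 12"), the same for VAS and OHIP-14 ("Differences and mean percentage change in the visual analogue scale (VAS) and 14-item Oral Health Impact Profile (OHIP-14")), and the same for the three scintigraphy parameters.

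Section 13.3.2.2 starts with a normality test and a log or square-root transformation where normality fails. It then fixes the comparison of the arms: "Specifically, an independent T test or Mann-Whitney U test will be performed to compare values between the two groups". A later bullet reads "The group and time interaction effect of repeated-measures data will be analyzed through repeated-measures analysis of variance (ANOVA) or ANCOVA", with GEE as a further alternative according to the nature of the data. That bullet names no covariate and does not choose among the models.

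The only conditional baseline adjustment in the protocol is in section 13.3.1.2 and concerns the primary outcome: "If there is a significant difference in baseline values between the two groups, repeated-measures analysis of covariance (ANCOVA) will be performed".

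Baselines exist for every secondary outcome. For SFR, section 10.2.1 says "Visit 2 (Week 0) is replaced by screening test", and section 10.2.2 does the same for VAS. Scintigraphy and OHIP-14 are taken at Visit 2 (sections 10.2.3 and 10.2.4).

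**The concern.** A t-test on change from baseline is a comparison in which the regression slope of follow-up on baseline has been fixed at 1. A t-test on the week-12 value fixes that slope at 0. ANCOVA estimates the slope from the data, so it leaves the least residual variance of the three. The protocol collects the baselines but names between-arm tests that do not use them in this way.

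What is at stake is the width of the intervals on the secondary outcomes. Section 4.4 hypothesises comparable relief of symptoms with fewer side effects. The primary outcome is a flow rate, so VAS and OHIP-14 carry the symptom part of that hypothesis. When the aim is to show similarity, an avoidably wide interval is a real weakness, because a non-significant t-test is easily misread as evidence that the arms are alike.

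**Working it through.** **Inputs from the protocol (sections 8.1 and 8.4).** Week-12 unstimulated SFR has a planning SD of 0.35, the margin is 0.21, one-sided alpha is 0.05, power is 90% and dropout is 20%. Entry requires "unstimulated SFR $\leq$ 0.25 ml/min", and 0.1 or less for Sjögren's syndrome. **Assumed, because not given:** the baseline-to-week-12 correlation r (0.3 to 0.7) and the baseline SD s0.

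**The plan's own figure.** The SD is √((0.48² + 0.13²)/2) = 0.352. The sample size is 2 × 0.35² × (1.645 + 1.282)²/0.21² = 47.6, so 48 per arm, and 48/0.8 = 60. Both reproduce. They belong to the primary outcome; the protocol states no power or precision for the secondary outcomes. I use 48 evaluable per arm as the yardstick.

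**General result.** With baseline SD s0 and week-12 SD s1, the per-patient variances are:
- change: s0² + s1² − 2·r·s0·s1
- week 12 only: s1²
- ANCOVA: s1²(1 − r²)

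Change minus ANCOVA is (s0 − r·s1)², which is never negative. Week 12 minus ANCOVA is r²·s1², also never negative.

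**Equal variances (s0 = s1 = s; variances in units of s²).** The loss of effective sample is (1 − r)/2 for change and r² for week 12 only.

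| r | Var change, 2(1−r) | Var ANCOVA, 1−r² | Loss, change | 48 per arm acts like | Loss, week 12 only | 48 per arm acts like |
|---|---|---|---|---|---|---|
| 0.3 | 1.40 | 0.91 | 35% | 31.2 | 9% | 43.7 |
| 0.5 | 1.00 | 0.75 | 25% | 36.0 | 25% | 36.0 |
| 0.7 | 0.60 | 0.51 | 15% | 40.8 | 49% | 24.5 |

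In interval width, the change score costs a factor √(2/(1+r)): 24%, 15% and 8% wider at r = 0.3, 0.5 and 0.7. A simulation with 48 per arm, which includes the price of estimating the slope, gave change-score losses of 24% at r = 0.5 and 14% at r = 0.7. That price is about one percentage point.

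**Unstimulated SFR.** Equal variances are not credible here. A value between 0 and 0.25 cannot have an SD above 0.125, against a planned week-12 SD of 0.35. The loss is 1 − s1²(1 − r²)/(s0² + s1² − 2·r·s0·s1) with s1 = 0.35:

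| r | s0 = 0.03 | 0.05 | 0.072 | 0.125 |
|---|---|---|---|---|
| 0.3 | 4.8% | 2.6% | 1.0% | 0.4% |
| 0.5 | 18.6% | 14.5% | 10.4% | 2.6% |
| 0.7 | 42.5% | 37.8% | 32.4% | 18.7% |

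For example, at r = 0.3 and s0 = 0.03 the change variance is 0.1225 + 0.0009 − 0.0063 = 0.1171, the ANCOVA variance is 0.1225 × 0.91 = 0.1115, and the loss is 4.8%. The loss vanishes where s0 = r·s1, which at r = 0.3 is 0.105. The pattern runs the other way from the equal-variance table: here the loss grows with r, because the fitted slope r·s1/s0 moves away from 1. At r = 0.7 that slope is 0.245/0.125 = 1.96 or more.

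This reversal leans on the SD of 0.35. With the cited placebo arm's SD of 0.13 and s0 = 0.125 the variances are nearly equal again, and the loss at r = 0.3 is 32.5%.

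**Does the interaction bullet fill the gap?** Scintigraphy is measured only at weeks 0 and 12. With two time points the group-by-time test in a repeated-measures ANOVA is the same as a t-test on change. For SFR, VAS and OHIP-14, with four time points, it tests whether the profiles differ; it does not in itself yield an adjusted week-12 difference.

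**The case against.** The other side has several good points.

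- **The baselines are not thrown away.** A reader might infer that they are. A change score uses them, with a slope of 1. Only the week-12 comparison of stimulated SFR ignores baseline, and its change is listed as a separate outcome. Nor are these only raw differences, since percentage changes and transformations are planned too.
- **Adjustment is not excluded.** Section 13.3.2.2 allows ANCOVA or GEE for repeated measures, and a SAP could settle the details. This stands. But the between-arm test is stated, not left open, and the model bullet names neither a covariate nor a week-12 estimate.
- **The size is unknown.** It is tempting to say that a quarter to a third of the sample is lost. That needs r of about 0.33 to 0.5 together with equal variances, and the protocol gives neither.
- **The entry limits do not make the loss large.** A reader might argue that capping baseline weakens its correlation with follow-up and so worsens the loss. The limits apply only to unstimulated SFR and VAS. For unstimulated SFR the same cap also shrinks the baseline variance, and under the planned SD a low r then means little loss.
- **The arithmetic covers the t-test only.** It does not cover the Mann-Whitney branch or percentage change, and skewed data need some provision. The cited trial's SD of 0.48 on a mean of 0.38 suggests that skewness is likely.

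**Conclusion.** The point holds as one of efficiency. The between-arm tests named for the secondary outcomes leave precision unused that the collected baselines could supply, and no other bullet restores it. With equal variances and r between 0.3 and 0.7, the loss is 15–35% of the effective sample for change scores and 9–49% for the week-12 stimulated SFR. For the change in unstimulated SFR it ranges from negligible to about 43%, given s1 = 0.35 and s0 between 0.03 and 0.125. All of these rest on assumed correlations and baseline SDs.

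Two stronger readings are not supported. Under randomisation the unadjusted comparisons are not biased; a chance baseline imbalance carries into the estimate only conditionally on having occurred. And the primary non-inferiority decision in section 13.3.1.2 is not affected, because it does not use these tests. The secondary outcomes have no stated power or decision rule, so this improves what the trial can report and does not correct an error that changes its main conclusion.

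**What to change.** In section 13.3.2.2, for each secondary outcome measured at baseline, name one between-arm analysis: an ANCOVA of the week-12 value on arm and the outcome's own baseline, reporting the adjusted difference with its 95% CI. Taking the change as the dependent variable, with baseline still in the model, gives the same arm effect, so the change endpoints of section 13.3.2.1 need not be abandoned.

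For clearly skewed outcomes, apply the planned log or square-root transformation to the week-12 and baseline values. Neither transformation is defined for a negative change. The log cannot take zeros either, so the square root is easier where zero readings occur. Alternatively, add a rank-based or robust analysis as a sensitivity check. Absolute and percentage change by arm can stay as descriptive summaries.

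The cost is a change of wording in the protocol, carried into any SAP; no visit, measurement or patient is added. The reported effect becomes a baseline-adjusted difference, and one slope is estimated per outcome.

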#### **13.4. Safety assessment**

- It includes adverse events, clinical laboratory examination, vital signs, and physical examination.
- Safety outcomes will be analyzed in the intention-to-treat (ITT) population, and the original data are analyzed without correction of the data.
- All test subjects' vital signs, physical examination, and clinical laboratory examination results are charted and comprehensively reviewed. The investigator confirms whether there is an abnormality in each test subject, writes its clinical significance, reviews whether it is related to the test drug, and presents the results of test subjects with significant clinically

Version 2.6

fluctuations in a separate table.

#### **13.4.1.1. Adverse events (AE)**

- Adverse events (AEs) are standardized into system organ class (SOC) and preferred term (PT) based on MedDRA ver. 23.1 (Korean).
- For AEs and drug reactions in this clinical trial, the frequency (number of test subjects), percentage, and number of occurrences are presented based on SOC and PT for each group.
- For serious AEs, the frequency, percentage, and number of occurrences are presented based on SOC for each group. Serious AEs are also summarized in a list of AEs, periods, courses, severity, outcomes, and causal relationships.
- In addition, individual lists of all test subjects with AEs are presented (including experimental/control group, reported AEs, start date/time and end date/time, course, intensity, seriousness, the association with clinical trial drugs, action taken, and final outcomes). AEs that caused discontinuation of the test are presented as a separate list. AEs are summarized using the preferred terms according to MedDRA ver. 23.1 (Korean).

#### **13.4.1.2. Vital signs, physical examination**

- The values measured at each visit and the changes from baseline test results are summarized in descriptive statistics (degree (N), median, mean, standard deviation (SD), minimum, and maximum values).

#### **13.4.1.3. Clinical laboratory examination**

- For continuous data (e.g., CBC, Clinical chemistry), the values measured at each visit and the changes from baseline test results are summarized in descriptive statistics (degree (N),

Version 2.6

median, mean, standard deviation (SD), minimum, and maximum values). For categorical data, baseline and each-visit values are summarized and described using frequencies.

## **14. Safety evaluation criteria and method, and reporting method**

### **14.1. Definition of safety-related terms**

#### **14.1.1. Adverse events (AEs)**

- Adverse event (AE) refers to an undesirable and unintended sign, symptom, or disease that occurs in the test subject receiving a drug used in a clinical trial, and does not necessarily have a causal relationship with the clinical trial drug. Therefore, AEs include undesirable and unintended signs or symptoms (e.g., clinically meaningful laboratory test value abnormalities) that appear or worsen during a clinical trial, regardless of the causal relationship with the clinical trial drug.

#### **14.1.2. Adverse Drug Reaction (ADR)**

- Adverse Drug Reaction (ADR) refers to all harmful and unintended reactions occurring at any dose of drug used in clinical trials, in which a causal relationship with a clinical trial drug cannot be excluded.

#### **14.1.3. Serious adverse events (SAEs)**

- Serious adverse events (SAEs) refer to cases that fall under each of the followings among AEs or ADRs that occurred during clinical trials.
  - Death or life-threatening events
  - Hospitalization or prolonged hospitalization of test subjects
  - Permanent or serious disability or loss of function
  - Congenital anomalies or birth defects

## 14.2. Evaluation of adverse events (AEs)

### 14.2.1. Criteria for evaluating the severity of AEs

- The investigator evaluates the severity of each AE and SAE reported during the trial period.

Severity is assessed in accordance with MedDRA ver. 23.1 (Korean).

| Grade |                                                                                                                                                                         |
|-------|-------------------------------------------------------------------------------------------------------------------------------------------------------------------------|
| 1     | Mild; asymptomatic or mild symptoms; clinical or diagnostic observations only; intervention not indicated.                                                              |
| 2     | Moderate; minimal, local or noninvasive intervention indicated; limiting age-appropriate instrumental ADL*                                                              |
| 3     | Severe or medically significant but not immediately life-threatening; hospitalization or prolongation of hospitalization indicated; disabling; limiting self care ADL** |
| 4     | Life-threatening consequences; urgent intervention indicated.                                                                                                           |
| 5     | Death related to AE.                                                                                                                                                    |

### 14.2.2. Evaluation of causality of AEs

- The criteria for evaluating the causal relationship with clinical trial drugs for AEs and SAEs are as follows.
- 1) Definitely related
  - Any evidence that this drug has been administered
  - When AEs are most probably explained by the administration of this drug than by other causes
  - Abnormal reactions disappear after discontinuation of administration
  - If the re-administration result is positive (re-challenge, only if possible).
  - If the AE is consistent with the information already known about this drug or other drug of the same class

## Version 2.6

- 2) Probably related
  - Any evidence that this drug has been administered
  - If the time order of administration of this drug and the onset of AEs is reasonable
  - When AEs are more likely to be explained by the administration of this drug than by other causes
  - Abnormal reactions disappear after discontinuation of administration
- 3) Possibly related
  - Any evidence that this drug has been administered
  - If the time order of administration of this drug and the onset of AEs is reasonable
  - When it is determined that AEs are due to administration of this drug at a similar level to other possible causes
  - Abnormal reactions disappear after discontinuation of administration
- 4) Probably not related
  - No evidence that this drug has been administered
  - If there are other more likely causes for AEs
  - If the result of discontinuation of administration is negative or ambiguous
- 5) Definitely not related
  - No evidence that this drug has been administered
  - If there is any other reason that most likely explains the AEs
  - If AEs are not lost as a result of discontinuation of administration
- 6) Unknown

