## Version 2.6

- From the start of clinical trial drug administration to the end of administration, the occurrence and grade of adverse events are evaluated at each visit.
- The basic principles of grading are as follows

Grade 1: Side effects that are symptomatic but do not require treatment

Grade 2: Side effects that require treatment to alleviate symptoms but do not interfere with activities of daily living (ADL) and do not pose a threat to life

Grade 3: Side effects that can be life-threatening if left untreated

Grade 4: Life-threatening side effects

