##### **13.1.3. Efficacy outcomes**

- Efficacy outcomes will be analyzed for both the per-protocol (PP) and ITT populations. In case of discrepancies between the efficacy outcomes of PP and ITT populations, both set of results will be presented and compared, with the PP population considered the main

Version 2.6

analysis and the ITT population as supplementary analysis.

- The ITT population consists of participants who received at least one dose of the clinical trial drugs and underwent efficacy evaluation more than once during the treatment period. In cases of missing values due to dropouts or discontinuation before the clinical trial ends, missing data from dropout participants will be imputed using the last observation carried forward analysis.
- The PP population is a subset of the ITT population. It includes participants who consumed >70% of the prescribed doses of clinical study drugs and completed follow-up visits and corresponding outcome measurements (weeks 4, 8, and 12) during the 12-weeks treatment periods. Participants falling under a 'significant violation of clinical trial plan' will be excluded from the PP population.

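### The causality criteria in protocol section 14.2.2 contradict themselves and the definition of an adverse drug reaction in 14.1.2, so the by-group drug reaction table is not reproducibly defined

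*Protocol*

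**What the plan says.** Section 14.2.2 of the protocol gives six causality categories for AEs and SAEs: definitely, probably and possibly related (1 to 3), probably and definitely not related (4 and 5), and Unknown (6, with no criteria).

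- Categories 1 to 3 each ask for evidence of dosing, and each lists "Abnormal reactions disappear after discontinuation of administration". Only rechallenge, in category 1, is qualified as applying where possible.
- Categories 4 and 5 each list "No evidence that this drug has been administered". Category 4 adds "If the result of discontinuation of administration is negative or ambiguous"; category 5 adds "If AEs are not lost as a result of discontinuation of administration".
- Nothing says whether all criteria in a category must hold.

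Section 14.1.2 defines an ADR as a harmful, unintended reaction "in which a causal relationship with a clinical trial drug cannot be excluded". Section 13.4.1.1 then uses the distinction: "For AEs and drug reactions in this clinical trial, the frequency (number of test subjects), percentage, and number of occurrences are presented", by system organ class, preferred term and group.

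Safety is analysed in the ITT population (13.1.2), and 13.1.3 says: "The ITT population consists of participants who received at least one dose of the clinical trial drugs", with a further condition on efficacy evaluation. On timing, 10.3.1 says: "From the start of clinical trial drug administration to the end of administration, the occurrence and grade of adverse events are evaluated at each visit".

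**The concern.** The criteria appear to fail for the people they will be applied to. A participant whose events are analysed has taken drug, so a criterion requiring no evidence of dosing cannot discriminate. Many events also occur in participants who carry on with treatment, for whom there is no result of stopping to assess.

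This matters because fewer side effects is one of the two parts of the objective (4.1). Causality is recorded for every AE (14.4.1), and drug reactions are tabulated by group. The trial is open-label (9.1), so investigators who have to improvise around unusable criteria will do so knowing the arm. These are instructions to investigators written into the protocol, not analysis detail that could be left to a later plan.

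**Working it through.** The plan gives no figure to reproduce; the check is one of logic.

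**Step 1: categories 4 and 5 against the safety population.** Category 4 requires no evidence of dosing together with a negative or ambiguous result of stopping. Category 5 requires no evidence of dosing together with persistence after stopping. A result of stopping presupposes dosing, so each category contradicts itself. By 13.1.3 everyone analysed for safety has had at least one dose, and by 10.3.1 AEs are evaluated from the start of administration.

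**Step 2: all criteria required.** Take a dosed participant and cross 5 levels of likely cause (drug most likely, drug more likely, equal, other more likely, other most likely) with 4 results of stopping (resolves, negative, ambiguous, not stopped or not assessed). This gives 5 × 4 = 20 combinations. Timing, rechallenge and consistency with known effects are taken as satisfied.

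| Likely cause | Resolves | Negative | Ambiguous | Not stopped or not assessed |
|---|---|---|---|---|
| Drug most likely | 1, 2 | none | none | none |
| Drug more likely | 2 | none | none | none |
| Equal | 3 | none | none | none |
| Other more likely | none | none | none | none |
| Other most likely | none | none | none | none |

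Only 3 of 20 combinations fit a category with criteria, and 0 of 20 fit category 4 or 5. The other 17 are left to Unknown. These are cells of a logic table, not expected frequencies of events.

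**Step 3: any one criterion sufficient.** Evidence of dosing is listed in categories 1, 2 and 3. Every event in a dosed participant then meets all three at once, and an event with a more likely other cause also meets category 4. The rule fails on this reading too.

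**Step 4: serious events.** Section 14.1.3 includes death and permanent disability among SAEs, and 14.2.2 applies to SAEs. Neither outcome can disappear on stopping. With all criteria required, a fatal or permanent reaction cannot be classed as related.

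**Step 5: against the ADR definition.** Section 14.1.2 turns on whether causality can be excluded and sets no condition about stopping. No passage says which of the six categories are ADRs. If ADR means 1 to 3, the all-required reading leaves out every reaction without an observed resolution after stopping. If it means 1 to 3 plus Unknown, the same reading makes every AE an ADR, because categories 4 and 5 are empty.

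**Step 6: how far each repair goes, still with all criteria required.**
- Removing the no-dosing criterion alone adds 2 causes × 2 results (negative, ambiguous) = 4 cells: 3 + 4 = 7 of 20. The 13 that fail include every case where drug was not stopped.
- Also applying the stopping criterion only where there is a result to assess adds the 5 cells of the last column: 7 + 5 = 12.
- The remaining 8 are drug at least as likely but no clear resolution (3 × 2 = 6), and another cause more likely but the event resolves (2). Evidence there is mixed or unclear, so the protocol must also say how criteria combine.

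**The case against.** The strongest reply is that 14.2.2 nowhere makes every criterion mandatory. It mixes conditional clauses with bare phrases, and the contradiction in categories 4 and 5 itself suggests they were meant as considerations to be weighed. An investigator using judgement would reach sensible ratings. This stands as far as it goes: the table in step 2 rests on an assumption the protocol neither states nor rules out. It does not rescue the section, because the literal alternative fails as well (step 3), and weighing without a stated rule is not reproducible between investigators.

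A reader might go further and infer that the criteria cannot be applied to treated participants at all, that ADR counts will be wrong, or that the drug reaction table merely tracks who stopped early and will differ between arms for that reason. The protocol does not support this.
- An event that resolves on stopping, with drug at least as likely a cause as any other, can be classed as related, and Unknown is always available.
- Equating ADR with categories 1 to 3 is a mapping the protocol never gives.
- Every completer stops at week 12. Section 4.5 gives a pilocarpine half-life within 3 hours, 14.4.1 records the date an event disappears, and 15.4 allows observation until it does, if necessary. Resolution after stopping can therefore be seen in some who continued to the end. On the other side, 10.3.1 ends routine evaluation with administration and 9.2 schedules no visit after week 12. How often the result will be known cannot be derived.

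It is also fair to say that the safety comparison can rest on all-causality AEs, which 13.4.1.1 tabulates by group, and that onward reporting under 14.4.2 turns on seriousness and unexpectedness, not on these categories.

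**Conclusion.** Section 14.2.2 is wrong as written. The no-dosing criterion in categories 4 and 5 is unusable in a dosed population and contradicts its neighbours; this needs no assumption. The consequence for categories 1 to 3 depends on how criteria combine, which is not stated: required jointly, they reach 3 of 20 combinations; taken singly, they admit every event. Combined with the ADR definition in 14.1.2 and the absence of any mapping, this leaves the by-group drug reaction table in 13.4.1.1 not reproducibly defined and open to misclassification in either direction.

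Neither the direction nor the size of any difference between arms can be estimated from the protocol. All-causality AE and SAE counts, SAE reporting and the primary outcome are untouched. It should be corrected, but it does not threaten the trial's main comparison.

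**What to change.** Amend 14.2.2 and tie it to 14.1.2:

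1. In categories 4 and 5, replace the no-dosing criterion with implausible timing relative to dosing, or a clearly more likely other cause.
2. In categories 1 to 5, make the criterion on stopping apply only where drug was stopped and the outcome could be assessed.
3. State whether the criteria in a category are joint and, if not, how they are weighed, including where the cause and the result of stopping point in different directions.
4. Limit Unknown to events with insufficient information, and state which categories count as ADRs, consistently with 14.1.2. Items 1 and 2 must come with this. If Unknown counted as an ADR while category 4 or 5 still required a result of stopping, an incidental injury in a participant who continued drug would become an ADR.

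Recording causality separately for pilocarpine and Baekhogainsam-Tang is optional.

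The cost is a wording change and re-coding of causality for AEs already entered. Because the trial is open-label, the re-coding should follow the new rule uniformly in both arms. There is no added burden on participants.
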